| L. Definition of the Study population All permanently-registered patients with research-standard data and incident type 2 diabetes Read codes from at least 1 year after 1^st^ January 2006 (start of follow-up; coinciding with when ethnicity was recorded for ≈80% of new registrations (17)) to 31^st^ December 2018 in the CPRD. The study will be restricted to incident cases to enable more precise measurement of treatment stage; people with prevalent type 2 diabetes Read codes prior to 2006 will be excluded.  Type 2 diabetes will be defined by a previously tested algorithm that uses Read codes, medication, blood test results and diabetes-specific process of care Read codes to adjudicate diabetes status (27) – see appendix. Specific exclusions will include: type 1 diabetes, gestational diabetes, non-specified diabetes diagnosed at ≤40 years in Europeans or ≤35 years in South Asians and African Caribbeans (reducing misclassified type 1 diabetes), and secondary diabetes (e.g. drug-induced).  In people without diabetes, those eligible for antihypertensive treatment will include people ≥40 years of age with incident: Read codes for hypertension, clinic BP of ≥160/100, ambulatory BP of ≥150/95 or clinic BP of ≥140/90 or ambulatory BP of ≥135/85 **plus either** 10 year CVD risk score exceeding 20% or 10% (for calendar years 2006-2013 and 2014-2019 respectively) **or** evidence of target organ disease (i.e. Read codes for left ventricular hypertrophy, chronic kidney disease, micro/ macroalbuminuria, or hypertensive retinopathy) (24). Those eligible for lipid-lowering medication will include people ≥40 years of age with an incident recording of CVD risk score ≥20% (if recorded between 2006 and 2013), or ≥10% (if recorded between 2014 and 2019), to account for guidelines changes (26)) during the study period. |

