| O. Data/ Statistical Analysis For all parts of the study, the population will be people with and without new-onset type 2 diabetes active in CPRD from 2006 (see section K, above) and the exposure will be ethnicity (either South Asian vs. European [baseline] or African Caribbean vs. European [baseline], as detailed in section L, above). Covariates in base models will include age and sex, and further covariates will be considered individually, as outlined in section vi) below. Statistical analysis is further considered by objective:   1. **Outcome:** Proportion of those eligible for primary prevention who are prescribed a) antihypertensives and b) lipid-lowering medication   **Entry:** Date of incident a) hypertension Read code/ raised BP reading or b) elevated 10 year CVD risk score, at least 12 months after study start date of 1^st^ January 2005  **Exit:** First of; date of first antihypertensive/ lipid-lowering medication prescription (defined by the absence of a prescription for the medication in the previous 6 months’ records), end of study, leaving CPRD practice or death  **Analysis:** Proportions receiving antihypertensives/ statin will be compared by ethnicity, then logistic regression models will be used to adjust for confounding/ investigate potential mediators  **Example effect measure:** Odds ratio (OR) of receiving an antihypertensive/ lipid-lowering medication vs. not for each ethnic group of interest, stratified by time period since identification of hypertension/ elevated CVD risk   1. **Outcome**: time to initiation of first-line anti-diabetic/ antihypertensive/ statin, probability of receiving anti-diabetic/ antihypertensive/ statin at one year post-diagnosis/ identification of high CVD risk   **Entry**: date of type 2 diabetes diagnosis/ incident hypertension Read code or raised BP reading/ incident high 10 year CVD risk score recording  **Exit**: date of first anti-diabetic/ antihypertensive/ statin prescription (defined by the absence of a prescription for the medication in the previous 6 months’ records), or end of study/ leaving CPRD practice/ death  **Analysis**: summary statistics will be compared by ethnicity using Kaplan-Meier time-to-event analysis (cumulative failure probability in a given time frame by ethnicity, comparison of medians by log-rank test), Cox proportional hazards regression models will be used to adjust for confounding/ investigate potential mediators  **Example effect measure**: hazards ratio (HR) for anti-diabetic/ antihypertensive/ statin prescription   1. **Outcome:** proportions of patients prescribed medication from each anti-diabetic (stratified by first- to third-line treatment), antihypertensive and lipid-lowering class (defined by the absence of a prescription for the medication in the previous 6 months’ records)   **Sub-population:** a) all participants starting first- to third-line anti-diabetic treatment, b) all patients on antihypertensives, or c) all patients on lipid-lowering medication  **Analysis:** proportions receiving each drug will be compared by ethnicity, then logistic regression models will be used to adjust for confounding/ investigate potential mediators  **Example effect measures**: odds ratio (OR) of being prescribed metformin (=1) vs. non-metformin medication (=0) at first stage of treatment, OR of being prescribed sulphonylurea (=1) vs. non- sulphonylurea medication (=0) at second stage of treatment, OR of calcium-channel blocking antihypertensive prescription vs. non- calcium-channel blocking antihypertensive in those on antihypertensive treatment, OR of statin prescription vs. non-statin lipid-lowering medication prescription in those with >10% 10 year cardiovascular risk   1. **Outcome:** proportions of patients prescribed each dose of each anti-diabetic, antihypertensive and lipid-lowering medication, stratified by treatment stage (defined by the absence of a prescription for the medication in the previous 6 months’ records)   **Sub-population:** a) all participants on first- to third-line anti-diabetic treatment, b) all patients on antihypertensives, or c) all patients on lipid-lowering medication  **Analysis: :** proportions receiving each dose of each drug will be compared by ethnicity, then logistic regression models will be used to adjust for confounding/ investigate potential mediators  **Example effect measures**: OR of being prescribed maximum dose (2g daily) vs. sub-maximum dose of metformin, OR of being prescribed atorvastatin 10mg per day vs. higher doses (20mg, 40mg or 80mg)   1. **Outcome:** yearly monitoring rate post commencement of medication from each anti-diabetic (first- to third-line), antihypertensive and lipid-lowering class – i.e. number of times HbA1c/ blood pressure/ blood lipids measured per person-year of follow-up, stratified by year after commencement; may be multiple entry dates per person for different medications   **Entry:** first use of any medications of interest from 2006 onwards  **Exit:** first of; end of strata (e.g. 1 year after medication commencement), end of study/ leaving CPRD practice/ death  **Analysis:** summary statistics will be compared by ethnicity, Poisson regression modelling used to adjust for confounding/ investigate potential mediators  **Example effect measures**: yearly monitoring rate ratios (RRs)   1. **Outcome:** time to medication intensification (up-titration, addition or switching) after detection of sub-optimal control of diabetes, hypertension or blood lipids, or probability of intensification 1 year post-detection of sub-optimal control; may be multiple entry dates per person for different medications   **Entry:** date when sub-optimal risk factor control detected (see section M for how this is defined for each risk factor)  **Exit:** first of; date of anti-diabetic, antihypertensive or lipid-lowering treatment intensification, end of study/ leaving CPRD practice/ death  **Analysis:** summary statistics will be compared by ethnicity using Kaplan-Meier time-to-event analysis (cumulative failure probability in a given time frame by ethnicity, comparison by log-rank test), Cox proportional hazards regression models will be used to adjust for confounding/ investigate potential mediators  **Example effect measures**: cumulative failure probability for each ethnic group 1 year post detection of sub-optimal value, comparison of median survival times using the log-rank test by ethnicity, HRs of intensification stratified by year   1. **Outcome:** influence of deprivation, polypharmacy, multi-morbidity, drug adherence (iv) and v) only), patient engagement with healthcare, diabetes duration and HbA1c on any ethnic differences found in i) to v).   **Entry:** as above for i), iv) and v)  **Exit:** as above for i), iv) and v)  **Analysis:** as above for i) to v)  **Covariates:** smoking status, BMI, deprivation, polypharmacy, multi-morbidity, drug adherence, patient engagement with healthcare, diabetes duration and HbA1c  **Effect measures:** we will observe the degree of attenuation of the ethnic difference effect measure for each outcome when each covariate is inserted in turn to models, and thus evaluate the likelihood of confounding or mediation  Sub-group/ sensitivity analyses  See section O of original application  Plans for addressing misclassification and bias  See section O of original application  Multiple comparisons  See section O of original application |

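### Objectives 1 and 2 apply the six-month prescription-free rule to the event but not to entry, so people already treated stay at risk and are scored as not initiated until a gap, switch or addition, or to the end of follow-up

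*Supplement*

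**What the plan says.** The current text is the amendment of 9 December 2019.

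- **Event.** In section O, objective 1 ends follow-up at the "date of first antihypertensive/ lipid-lowering medication prescription (defined by the absence of a prescription for the medication in the previous 6 months’ records". Objective 2 uses the same rule: "date of first anti-diabetic/ antihypertensive/ statin prescription (defined by the absence of a prescription for the medication in the previous 6 months’ records". The only other exits are end of study, leaving the practice and death.
- **Entry.** For objective 1 it is given as "Date of incident a) hypertension Read code/ raised BP reading or b) elevated 10 year CVD risk score, at least 12 months after study start". For objective 2 it is the "date of type 2 diabetes diagnosis/ incident hypertension Read code or raised BP reading/ incident high 10 year CVD risk score recording".
- **Eligibility.** In section L, for people without diabetes, "those eligible for antihypertensive treatment will include people ≥40 years of age with incident: Read codes for hypertension, clinic BP of ≥160/100" opens the antihypertensive definition. For lipids, "Those eligible for lipid-lowering medication will include people ≥40 years of age with an incident recording of CVD risk score ≥20" per cent, or 10 per cent for later calendar years.
- **Exclusions.** Section L begins its list with "Specific exclusions will include: type 1 diabetes, gestational diabetes, non-specified diabetes diagnosed at ≤40 years in Europeans" and continues with diabetes type and cause. Prevalent diabetes is removed by Read code. Prior or current use of the drugs under study is not mentioned.

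The bias text carried over from the original application deals with prescriptions issued in secondary care. It does not deal with people already treated at entry.

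**The concern.** The word incident qualifies the code, the reading or the score. It does not qualify treatment. A risk score can be recorded for the first time in someone already taking a statin, and a first raised reading can occur in someone already on a blood-pressure drug. Such a person, if treated continuously, has no post-entry prescription preceded by six drug-free months, so cannot meet the event definition. In objective 1 they count as not prescribed. In objective 2 they remain in the risk set without an event.

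Objectives 1 and 2 ask whether minority ethnic groups are started on treatment less often or later. If one group has more people already treated at entry, these rules tend to make that group appear under-treated, which is the very finding the study is looking for. Age and sex adjustment does not remove this, and a larger sample does not shrink it.

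**Working it through.** **1. What denominator did the plan intend?** The amendment's feasibility counts expect at least 94K European, 6K South Asian and 3K African Caribbean antihypertensive initiators without diabetes. The sample size section takes 21% of eligible people as untreated. Eligible = initiators / (1 − 0.21):

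- Europeans: 94 / 0.79 = 119.0K (stated 119.4K)
- South Asians: 6 / 0.79 = 7.6K (stated 7.6K)
- African Caribbeans: 3 / 0.79 = 3.8K (stated 3.8K)

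The figures reproduce up to rounding. The planned denominator therefore holds initiators plus never-treated people, and nobody already on treatment. Section E also frames objective 1 as people being started or commenced on treatment. The entry and eligibility rules do not produce that population.

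**2. Inputs for the size of the bias.** The proportions p are the plan's own and are used illustratively: 24% (statin receipt at high risk), 42% (anti-diabetic at one year) and 79% (complement of 21% untreated). Only the 42% is stated as a one-year initiation figure. The share already treated at entry, q, is not in the documents and is assumed. The true ethnic difference is set to none.

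**3. Odds ratio, worst case.** If already-treated people never score an event, the observed proportion is p(1 − q). For p = 0.79 and q = 10% vs 20%, this is 0.711 vs 0.632, and OR = (0.632/0.368) / (0.711/0.289) = 0.70.

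**4. Hazard ratio.** Untreated people initiate at rate λ = −ln(1 − p), i.e. 0.274, 0.545 or 1.561 per year. Already-treated people score a restart, switch or addition at rate h. In each group S(t) = (1 − q)e^(−λt) + q·e^(−ht). Censoring is uniform over 1 to 9 years. The HR is the large-sample solution of the Cox score equation with equal group sizes.

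| p | q (reference vs minority) | OR, h = 0 | HR, h = 0 | HR, h = 0.10 | HR, h = 0.30 |
|---|---|---|---|---|---|
| 24% | 5% vs 10% | 0.93 | 0.91 | 0.95 | 1.00 |
| 24% | 10% vs 15% | 0.93 | 0.91 | 0.95 | 1.00 |
| 24% | 10% vs 20% | 0.86 | 0.82 | 0.91 | 1.01 |
| 42% | 5% vs 10% | 0.92 | 0.89 | 0.92 | 0.97 |
| 42% | 10% vs 15% | 0.91 | 0.89 | 0.92 | 0.97 |
| 42% | 10% vs 20% | 0.83 | 0.79 | 0.86 | 0.94 |
| 79% | 5% vs 10% | 0.82 | 0.86 | 0.88 | 0.91 |
| 79% | 10% vs 15% | 0.83 | 0.88 | 0.89 | 0.92 |
| 79% | 10% vs 20% | 0.70 | 0.77 | 0.80 | 0.85 |

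Finite-sample simulation gives essentially the same ranges: HR about 0.78 to 0.92 and OR about 0.71 to 0.95 in the worst case, and HR about 0.80 to 1.02 with later events. With q = 0 in both groups the HR returns to about 1.0.

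**5. Against the plan's detectable effects.** Table 1 gives HR 1.02 for antihypertensive initiation and 1.03 for anti-diabetic initiation. For statins it gives 1.15 (South Asian) and 1.18 (African Caribbean).

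- Antihypertensives: 90% power at the planned group sizes detects 79% vs 77.4% (South Asian) or 76.8% (African Caribbean). A gap in q of 1.58/79 = 2.0 points or 2.21/79 = 2.8 points produces that on its own when nobody in the reference group is already treated and h = 0.
- Statins: a 5-point gap gives an inverse OR of 1/0.93, about 1.07, and an inverse HR of 1/0.91, about 1.10. Both are below the stated limits. In the worst case, 10% vs 20% gives 1/0.86 = 1.16 and 1/0.825 = 1.21.

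**The case against.** The strongest reply is that the plan is silent rather than wrong. Its language points to new users, objective 1 is confined to primary prevention, and its counts leave no room for people already treated. A sensible analyst might exclude them. That is fair evidence of intent. It does not settle the matter, because the written entry and exit rules, applied as they stand, keep these people in. Another analyst could follow them to the letter and obtain a different ethnic contrast.

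A reader might infer that everyone already treated is scored as untreated for the whole of follow-up. The documents do not support that. A restart after six months without a prescription counts as a first prescription. If the medication means an individual drug, so does a switch or an added agent. These are false or misdated events from the same gap, and they pull the HR back towards 1. Where their rate exceeds the true initiation rate (0.30 vs 0.274 per year at p = 24%), the bias disappears or slightly reverses.

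A reader might also infer that the bias exceeds every detectable effect in Table 1. It does not: with a 5-point gap the statin results stay inside the stated limits of 1.15 and 1.18.

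It also stands that the share already treated, and any ethnic gap in it, are assumed. For diabetes, the adjudication algorithm uses medication as well as codes, and its diagram is not shown. How it dates someone prescribed metformin shortly before the diagnosis code cannot be judged.

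**Conclusion.** The point holds as a defect in the operational definition. The six-month rule governs the event only, no treatment-free condition governs entry or eligibility, and the result contradicts the plan's own objective and denominators.

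The size is conditional on assumed shares. For 5% vs 10% up to 10% vs 20% already treated and no true difference, the worst case is HR about 0.77 to 0.91 and one-year OR about 0.70 to 0.93. With restarts or switches at 0.10 to 0.30 per year, HR is about 0.80 to 1.01. Most bias arises where initiation is high, as for antihypertensives, and least for statins. If the already-treated share is the same in all groups, the absolute proportions are too low but there is little spurious ethnic contrast. The documents do not say which case applies, so the rule should be settled before analysis.

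**What to change.** In sections L and O, for objectives 1 and 2:

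- Make it an eligibility condition that there is no prescription for any drug of the relevant class (anti-diabetic, antihypertensive, lipid-lowering or statin) in the six months before entry. This is the plan's own window.
- Define the medication at class level for the first-prescription event, so that a switch or addition within a class is not counted as initiation.
- Count a first class prescription on the entry date as an event at day 0.
- Report the number excluded by ethnicity, which also shows how large the problem would have been.

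If first prescriptions shortly before the qualifying record are to count as day-0 events, write that as an explicit exception to the exclusion, or run it as a sensitivity analysis. Otherwise the same person would be both excluded and counted.

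The cost is a few lines of text, one extra derivation step and a somewhat smaller cohort. No new data are needed.

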| Technical Summary (Max. 300 words) UK South Asian and African Caribbean people with type 2 diabetes experience worse diabetic control and more cardiovascular complications than the European-origin population; ethnic minority populations without diabetes also experience an excess of most types of cardiovascular disease. Explanations are unclear. Blood pressure and lipid control, crucial to cardiovascular risk reduction for people with and without diabetes, also differ by ethnicity. However, ethnic differences in prescribing for diabetes, hypertension and hyperlipidaemia remain understudied.  Ethnic differences in prescribing anti-diabetic (in people with diabetes), antihypertensive and lipid-lowering medication (in people with and without type 2 diabetes) will be sought, including: i) time to commencement ii) choice of medication, iii) dosage, iv) monitoring and iv) time to intensification (either medication up-titration, addition or class switching) after detection of sub-optimal control.  Primary care electronic medical records will be used. Established algorithms and code lists will define ethnicity, diagnoses and medication use. Data will be analysed using Kaplan-Meier time-to-event methods and logistic, Poisson and Cox regression models (according to outcome), with South Asian or African Caribbean ethnicity as the exposure (baseline category=European). These methods will allow for differences in follow-up time. The potentially confounding or mediating influences of age, sex, smoking, BMI, deprivation, polypharmacy, multi-morbidity, drug adherence, patient engagement and diabetes duration/ HbA1c will be explored. |
| D. Outcomes to be Measured Proportion of people eligible for antihypertensive or lipid-lowering medication who are prescribed the respective medication; Time to first anti-diabetic/ antihypertensive/ lipid-lowering medication prescription; Choice of anti-diabetic/ antihypertensive/ lipid-lowering medication; Dose of anti-diabetic/ antihypertensive/ lipid-lowering medication; Monitoring of anti-diabetic/ antihypertensive/ lipid-lowering medication; Time to anti-diabetic/ antihypertensive/ lipid-lowering treatment intensification. |

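### Objective 1 fits logistic regression to a prescribed yes/no outcome with no fixed window or censoring rule, so any difference in follow-up between ethnic groups could pass as a prescribing difference

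*Supplement*

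**What the plan says.** All references are to the amendment of 9 December 2019 unless stated.

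- **Outcome (section O, objective 1):** "Proportion of those eligible for primary prevention who are prescribed a) antihypertensives and b) lipid-lowering medication". No time window is attached.
- **Entry:** the date of the qualifying blood pressure or hypertension record, or of the raised risk score, "at least 12 months after study start date of 1^st^ January 2005". Entry dates therefore vary from 2006 onwards.
- **Exit:** the first of first prescription, "end of study, leaving CPRD practice or death". Observation thus stops at a different point for each person.
- **Method for comparing the groups:** "Proportions receiving antihypertensives/ statin will be compared by ethnicity, then logistic regression models will be used to adjust for confounding/ investigate potential mediators". No weighting or offset is mentioned.
- **Measure offered as an illustration:** an odds ratio for each ethnic group, "stratified by time period since identification of hypertension/ elevated CVD risk". Stratum widths are not given. Nor is the handling of people whose observation ends untreated inside a stratum.
- **Adjustment:** "Covariates in base models will include age and sex". No term for length of follow-up is mentioned.
- **Objective 2:** initiation after the same index events is analysed by "Kaplan-Meier time-to-event analysis (cumulative failure probability in a given time frame by ethnicity, comparison of medians by log-rank test), Cox proportional hazards regression models", and the probability of treatment at one year is named as an outcome.
- **Technical Summary:** after listing Kaplan-Meier, logistic, Poisson and Cox methods together, it states: "These methods will allow for differences in follow-up time".

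**The concern.** A yes/no outcome has a clear meaning only if everyone is observed for the same time or if censoring is handled. Here, someone who leaves the practice untreated after three months could be counted exactly like someone untreated for ten years. Logistic regression on that outcome mixes how quickly people are prescribed with how long they are watched.

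If one ethnic group moves practice more often, or enters later in the study period, it would look under-treated even with identical prescribing rates. In a study of ethnic inequality in prescribing, that is the error most worth excluding.

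The other time-dependent objectives are protected. Monitoring is counted per person-year within defined yearly strata, and objectives 2 and 6 use time-to-event methods. Objective 1 has no equivalent safeguard, so the Technical Summary's general statement does not hold for it.

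**Working it through.** **1. The plan's own figure.** Table 1 gives detectable effects of 1.15 (South Asian, 3K vs 49K) and 1.18 (African Caribbean, 2K vs 49K) for statin receipt, labelled HR. The base proportion is 24%. I took alpha as 0.05 two-sided and read the 0.90 labelled beta as power.

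- Two-proportion formula, pooled variance: detectable proportions 0.2664 and 0.2721, i.e. odds ratios 1.150 and 1.184. This reproduces the plan.
- Schoenfeld formula with 24% events: HR 1.132 and 1.163. This does not.

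The stated figures are therefore odds ratios for a simple proportion with no follow-up term. Inverted, they are 1/1.15 = 0.87 and 1/1.18 = 0.85.

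**2. Simplest check of the mechanism.** Take equal hazards, fixed follow-up T in one group and fT in the other. Then p1 = 1 − (1 − p0)^f, and OR = odds(p1)/odds(p0).

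- p0 = 0.24: f = 0.9 gives p1 = 0.219, OR 0.89; f = 0.8 gives p1 = 0.197, OR 0.78.
- p0 = 0.79: f = 0.9 gives p1 = 0.754, OR 0.82; f = 0.8 gives p1 = 0.713, OR 0.66.

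These apply only to an odds ratio over the whole follow-up.

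**3. Dependence on the window.** Inputs from the plan: 24% receiving statins, and 79% on antihypertensives (100% less the 21% untreated), both in the sample size section. Assumed, because the documents give no follow-up by ethnicity:

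- a constant prescribing hazard λ, the same in both groups;
- administrative follow-up uniform over 0 to 13 years;
- exponential loss with mean μ = 10 years in Europeans and 6 years in the comparison group;
- people censored untreated within the window counted as not prescribed.

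The probability of remaining under observation to time t is G(t) = (1 − t/13)·exp(−t/μ). Mean follow-up is the integral of G: 4.40 years for μ = 10 and 3.55 years for μ = 6. The ratio is 0.81, i.e. 19% shorter.

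The proportion counted as prescribed by time w is P(w) = ∫₀ʷ λ·exp(−λt)·G(t) dt. Setting P(13) in Europeans to 0.24 or 0.79 gives λ = 0.0679 or 0.696 per year.

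| Window from eligibility | 24% case: P, European vs comparison | OR | 79% case: P, European vs comparison | OR |
|---|---|---|---|---|
| 1 year | 0.0602 vs 0.0583 | 0.97 | 0.464 vs 0.451 | 0.95 |
| 2 years | 0.107 vs 0.101 | 0.93 | 0.657 vs 0.626 | 0.88 |
| 5 years | 0.192 vs 0.169 | 0.86 | 0.782 vs 0.729 | 0.75 |
| Whole follow-up | 0.240 vs 0.199 | 0.79 | 0.790 vs 0.735 | 0.74 |

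The true hazard ratio is 1.00 in every row.

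**4. Range.** With μ = 8, 6, 5 and 4 in the comparison group, the follow-up ratios are 0.92, 0.81, 0.73 and 0.64.

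- Whole follow-up, 24% case: OR 0.91, 0.79, 0.71, 0.62.
- Whole follow-up, 79% case: OR 0.88, 0.74, 0.65, 0.55.
- One year, 24% case: OR 0.99, 0.97, 0.95, 0.93.
- One year, 79% case: OR 0.98, 0.95, 0.93, 0.89.

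**5. After repair.** In simulation under the same assumptions, a one-year outcome restricted to people with a full year of potential follow-up gave odds ratios of 0.99 to 1.00 throughout.

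**The case against.** The strongest reply is that objective 1 never specifies an ever/never odds ratio. Its example measure is stratified by time since identification, and with one-year strata most of the bias goes: at 19% shorter follow-up the statin odds ratio is 0.97, well inside the 0.85 to 0.87 threshold. That stands as far as it goes. But the stratification is offered only as an example and is not attached to the crude proportions. Its widths are undefined, and width decides the size of the bias. The plan is also silent on how people censored within a stratum are counted. Treating them as unprescribed is my assumption, not the plan's stated rule.

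Second, objective 2 already gives a censoring-aware analysis of the same initiation events. That stands, and it makes the repair cheap. It does not correct the odds ratio that objective 1 would report, and no rule says which result prevails if they disagree.

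Third, the original application's section O, which the amendment carries forward, stratifies by age group and calendar time. With age and sex in the base models, this deals with part of any difference due to entry date or mortality. Leaving the practice remains unaddressed.

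A reader might infer that the plan will produce a false ethnic disparity in its main result. The documents do not support that. They nowhere report that follow-up differs by ethnicity, and they name no primary objective. The constant hazard is also assumed: if initiation clusters soon after identification, later differences in follow-up would matter less.

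**Conclusion.** The concern holds in conditional form. As written, objective 1 has neither a fixed window nor a censoring rule, and the Technical Summary's claim about follow-up is not met by this logistic analysis. Whether bias follows depends on follow-up differing between groups, which is plausible but undocumented. Its size depends on strata that the plan leaves open.

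Under equal hazards and 19% shorter mean follow-up, the spurious odds ratio at 24%/79% prescribed runs from about 0.97/0.95 for one year to 0.79/0.74 for the whole follow-up. For statins, narrow strata keep it well short of the detectable effect; five years brings it to about that size, and the whole follow-up takes it beyond. This is a gap to close before analysis. It does not show that the planned results are wrong.

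**What to change.** 1. Define the objective 1 outcome as first prescription within a fixed 12 months of eligibility.
2. Then do one of the following:
   - fit the logistic model only in people whose entry date and registration allow the full 12 months; or
   - take the 12-month proportion by ethnic group from the one-year Kaplan-Meier estimate already planned in objective 2.
3. If longer periods are also reported, state the strata and how people censored within each are counted. Do not report an unstratified ever/never odds ratio.
4. Reword the Technical Summary so that its statement on follow-up covers logistic regression only on these terms.
5. Tabulate follow-up time and reason for exit by ethnic group, so that readers can judge the assumption.

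**Cost:** wording and modest programming, since objective 2 needs the same entry and exit dates. The restricted logistic model also loses people. In the assumed scenario the share with 12 months of potential follow-up is (12/13)·exp(−1/10) = 0.84 in Europeans and (12/13)·exp(−1/6) = 0.78 in the comparison group, so about 16% and 22% would drop out. The objective 2 route keeps everyone, so it is the better choice if the real loss is of that order.
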